### Objectives

#### Aim 1: Human-Centered Development of an English/Spanish Smoking Cessation Web App

We will develop iterative versions of a digital smoking cessation tool (a Web app with text messaging components) that is highly responsive to the needs and preferences of low-income English- and Spanish-speaking smokers. Development will take place with systematic input from patients who are part of the SFHN, which serves 70,000 mostly low-income individuals.

#### Aim 2: Improvement of Dissemination Strategies

Input from SFHN patients will identify effective ways of reaching and encouraging low-income English- and Spanish-speaking smokers to use the digital smoking cessation interventions that are developed. This information will support ongoing dissemination and implementation efforts beyond the grant period.

#### Aim 3: Evaluation of Resulting Smoking Cessation Web App

We will evaluate the effectiveness of the successive versions of the resulting stop smoking Web app by recruiting smokers at two levels—within the SFHN and throughout the state of California—culminating in an online RCT. Increased effectiveness will be defined as increased use of the Web app and higher abstinence rates than those obtained by a baseline (usual care) Web app.

#### Hypotheses

H1: Utilization of the final smoking cessation Web app (number of screens viewed, time spent using app, and amount of data entry) will be significantly higher than that of the baseline Web app.

H2: Recruitment based on dissemination strategies derived from ethnographic interviews will reach a significantly higher number of participants for successive online studies.

H3: Abstinence rates (7-day self-reported abstinence) will be significantly greater for the final Web app than for the baseline Web app.

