Estimates of how many SFHN patients use digital technology stem from a published report by Schickedanz et al [25] who surveyed 416 patients in waiting rooms of SFHN clinics and report that 71% were interested in using electronic communication with health care providers and 19% were already doing so. The survey was conducted in English, Spanish, Cantonese, and Mandarin; 87% (52/60) of Spanish speakers were interested in using email to communicate with their health care provider compared to 77% (164/213) of English speakers, 38% (23/61) of Cantonese speakers, and 75% (38/51) other. It appears, then, that interest in digital tools is high even in this low-income population. We have chosen to recruit SFHN patients who own smartphones because we believe that by 2018 most will do so and we want our intervention to be relevant for that time.

We propose to recruit the following number of SFHN smokers who use smartphones: face-to-face field studies (ethnographies and usability tests), 30 in year 1 and 30 in year 2 and online studies, 50 in year 1, 100 in year 2, and 200 in year 3. We believe recruiting 410 out of more than 8000 smokers over a 3-year period is feasible.

We will also be doing open recruitment of smokers who own smartphones throughout California at the following rate: 100 in year 1, 200 in year 2, and 800 in year 3. This effort will provide a large enough sample to carry out adequately powered outcome studies as described in the Methods section.

The proposed study is based on the premise that we cannot presume to know what would be best for our intended users without engaging them. To build a smoking cessation intervention that will be used and be effective with low-income smokers aged 18 years and older, including Spanish-speaking smokers, we must build a deep understanding of their needs and values.

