#### Online Studies

##### Online Study 1: Baseline (Usual Care) Web App

A Web app will be developed to test the data-gathering infrastructure for the subsequent apps and generate baseline information on four variables: recruitment rates, utilization of the app, follow-up completion rates, and quit rates. Usual care is described in the Intervention section. We will engage in focused recruitment of smokers from the SFHN (up to 25 English speakers and 25 Spanish speakers) as well as open online recruitment with California as our main target (up to 50 English speakers and 50 Spanish speakers). We will implement follow-up interviews to examine quit rates at 1, 2, and 3 months after enrollment in the study. We will use 3 text messages (identified as coming from the Stop Smoking Study) 2 days apart. The first question will ask “Have you smoked 1 or more cigarettes in the last seven days?” A no response will be interpreted as 7-day point prevalence abstinence. Additional questions will address 30-day abstinence, number of cigarettes smoked daily if not abstinent, and use of other smoking cessation tools.

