##### Online Study 2: Version 1.0

We will implement the same procedure as Online Study 1. We will obtain suggestions from our field test participants as to how to increase recruitment rates, for example, by modifying the wording in our social media announcements, the themes we touch upon in our radio and television interviews, the flavor of our public service announcements, word-of-mouth recruitment, the use of text messages to encourage enrollment, the wording of our search engine ads, and so on. We will use “tokens,” as described below, to identify how the participant heard about the Web app. We will examine which of these sources yield the greatest increases in recruitment. We will also track overall recruitment, as measured by the speed with which we meet our recruitment goals.

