##### Online Study 3: Version 2.0

We will repeat the procedure as in Online Studies 1 and 2.

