##### Online Study 4: Randomized Controlled Trial

We will carry out an RCT comparing the final version of the San Francisco Stop Smoking Web App with the baseline Web app. The RCT will be powered to detect differences in utilization rates and 7-day point prevalence quit rates, as described in the Data Analysis section. We will carry out open online recruitment, with a target of 800 smokers (400 English speakers and 400 Spanish speakers), as well as focused SFHN recruitment, with a target of 200 smokers (100 English speakers and 100 Spanish speakers).

Open recruitment will focus on California smokers. We will target English- and Spanish-speaking smokers searching for information on smoking cessation online using social media recruitment efforts, appearances on radio and television shows (especially those likely to be watched by Latinos), and a limited amount of search engine ads. To target the latter, we will use information reported by Graham and others [39] in terms of the most cost-effective online sites to recruit Latinos. We will focus our recruitment advertising resources on areas of California that have large proportions of Latinos in order to oversample Spanish-speaking smokers.

SFHN recruitment involves providing fliers for patients in waiting rooms at the San Francisco General Hospital clinics. Waiting room staff will also be given the fliers so they can inform smoking patients about the study. Primary care physicians will be provided with Post-It–like prescription pads which will have information regarding how to obtain the smoking cessation Web app. We will provide tokens (code numbers) to be entered when the Web app is installed that will indicate the source of the referral in order to determine whether physician recommendations to use the Web app result in greater utilization and higher quit rates than standard fliers. These tokens will also distinguish SFHN users from users recruited via open online recruitment.

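### H2 is worded as a count of participants, but enrolment in each online study is bounded by a preset cap or target; it should be restated as a recruitment rate, which the Methods already name

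*Protocol article*

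**What the plan says.** The Hypotheses section states H2 as a prediction that recruitment by strategies drawn from the ethnographic interviews "will reach a significantly higher number of participants for successive online studies".

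The size of each online study is set elsewhere in the article:

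- **Online Study 1:** from the San Francisco Health Network (SFHN), "up to 25 English speakers and 25 Spanish speakers"; from open recruitment, "up to 50 English speakers and 50 Spanish speakers".
- **Online Study 2:** "We will implement the same procedure as Online Study 1".
- **Online Study 3:** "We will repeat the procedure as in Online Studies 1 and 2".
- **Online Study 4 (the randomised trial):** open recruitment "with a target of 800 smokers (400 English speakers and 400 Spanish speakers"), plus a target of 200 from the SFHN. The Data Analysis section for Online Study 4 explains that the 800 is the minimum from the power analysis.
- **Yearly plan (Clinical Problem):** open recruitment of "100 in year 1, 200 in year 2, and 800 in year 3", and SFHN online recruitment of 50, 100 and 200 in the same years.

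The Methods describe recruitment differently from H2. The Online Study 1 section lists recruitment rates among the baseline variables. The Online Study 2 section says: "We will also track overall recruitment, as measured by the speed with which we meet our recruitment goals". It also plans to use tokens to compare referral sources. The Data Analysis section for Online Studies 1, 2 and 3 says that successive changes in recruitment rates will be examined.

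**The concern.** A count of participants measures dissemination only if it is free to respond to dissemination. Here the count cannot pass 150 in any of the first three studies, and in the fourth it is steered towards a number chosen to power the utilisation comparison. Once Study 1 is nearly full, better strategies in Studies 2 and 3 cannot show up as a higher count. In Study 4 a much higher count is expected because the target is much higher.

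H2 is one of three stated hypotheses and the only one about recruitment. An analyst who followed its wording could report no gain across Studies 1 to 3 and a large gain at Study 4, with both results coming mainly from the planned sizes. The findings on dissemination are meant to guide work beyond the grant period, so this reading matters to later users even though it does not touch the trial's efficacy result.

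**Working it through.** **Step 1. Planned sizes, and a check against the article's own totals.**

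- Study 1: 25 + 25 (SFHN) + 50 + 50 (open) = 150, an upper limit.
- Studies 2 and 3: same procedure, so 150 each, or 300 together. The yearly plan gives 100 + 200 = 300 for year 2, which agrees.
- Study 4: 800 + 200 = 1000, a target. The yearly plan gives 200 + 800 = 1000 for year 3, which agrees.
- SFHN total: 30 + 30 (field studies) + 50 + 100 + 200 (online) = 410, the figure stated in the Clinical Problem section. It reproduces exactly.

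**Step 2. Ratios to Study 1 if every limit is filled.**

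| Study | Count | Ratio |
|---|---|---|
| 2 | 150 | 150/150 = 1.0 |
| 3 | 150 | 150/150 = 1.0 |
| 4 | 1000 | 1000/150 = 6.7 |

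These are ratios of planned sizes, not forecasts of enrolment.

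**Step 3. How far the limits constrain a count comparison when they are only partly filled.** The article states no test for H2. As a yardstick I used the exact conditional test of two Poisson counts: given the total a + b, the larger count is binomial with probability 0.5 under no difference (two-sided, 5% level).

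- Study 2 or 3 at its cap of 150, against Study 1:
  - Study 1 = 100: p = 0.002
  - Study 1 = 117: p = 0.04998
  - Study 1 = 118: p = 0.058
  - Study 1 = 130: p = 0.26
- Study 4 against an earlier study filled to 150:
  - Study 4 = 186: p = 0.056
  - Study 4 = 187: p = 0.0497

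So if Study 1 enrols 118 or more of its 150, no count that Study 2 or 3 is allowed to reach can be significantly higher. Conversely, Study 4 could stop at 187, missing its target by (1000 − 187)/1000 = 81%, and still have a significantly higher count than a filled earlier study. This raw count takes no account of how long recruitment lasted.

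**Step 4. The same enrolment expressed as a rate.** The timeline figure is not shown, so the durations below are assumptions for illustration. With T1 and T2 the recruitment times and 150 enrolled in each study, the rate ratio is (150/T2)/(150/T1) = T1/T2.

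| Study 1 | Later study | Rate ratio | p |
|---|---|---|---|
| 150 in 6 months | 150 in 6 months | 1.0 | 1.0 |
| 150 in 6 months | 150 in 5 months | 1.2 | 0.12 |
| 150 in 6 months | 150 in 4 months | 1.5 | 0.0005 |
| 150 in 6 months | 150 in 3 months | 2.0 | <0.0001 |

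For Study 4, suppose an earlier study enrols 150 in 3 months, or 50 per month. Then 1000 enrolled in 12, 20 or 24 months is 83, 50 or 42 per month. The rate can be higher, equal or lower, although the count ratio is 6.7 in all three cases.

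**The case against.** The strongest reply is that the figures are ceilings and targets, and neither enrols anyone. A reader might infer that H2 is fixed in advance, true or false whatever the dissemination strategies do. The article does not support that. The Study 1 limits are upper bounds, the Study 4 numbers are goals, and any of them may be missed. Step 3 shows that a Study 1 shortfall to 100 against a filled later study would be a detectable difference. Reaching 1000 in year 3 would also be a real recruitment achievement compared with 150 in year 1. This part of the reply stands, and the point is therefore conditional on how full the studies are.

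The second reply is that H2 is one line in an Objectives section and the Methods put it into operation properly, through recruitment rates, speed and tokens. A cap on the total also does not fix the split by referral source. This is largely right as to substance: the suitable measure is already in the article. It does not remove the mismatch, because the hypothesis still names a different quantity from the one the Methods track, and only one of the two can respond freely under a cap.

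Third, the first three online studies are described as quality improvement, Aim 2 sets no count, and the choice of test can be left to an analysis plan. That is fair. The absence of a specified test for H2 is not part of this point.

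**Conclusion.** The point holds in a conditional form. H2 is stated as a number of participants, while the article bounds that number at 150 in each of Studies 1 to 3 and aims for 1000 in Study 4, mostly for reasons of power. If these limits are substantially filled, the ratios to Study 1 are about 1.0, 1.0 and 6.7 by plan, and the comparison says little about dissemination. If they are not filled, the count carries some information.

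The thresholds of 118 in Study 1 and 187 in Study 4 rest on a Poisson yardstick at the two-sided 5% level and on the other study being at 150. The durations in the rate illustration are assumed. None of this affects the randomised comparisons for H1 and H3 or their sample sizes. The issue is worth correcting because it changes what can be concluded about dissemination.

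**What to change.** Restate H2 as a higher recruitment rate in successive online studies: enrolments per unit of recruitment time, reported by source token and by recruitment stream (SFHN and open). This brings the hypothesis into line with the Online Study 1 and 2 sections and with the Data Analysis section for Online Studies 1, 2 and 3. Say plainly that it is a non-randomised before-after comparison, and that the rate also depends on how much recruitment effort is made in each period.

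The cost is small: a rewording of H2 and a record of when recruitment opens and closes in each study. Tokens are already planned. The choice of rate model can be left to the analysis plan.

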## Methods

### Conceptual Foundations of the Research Design

#### Design Thinking and Health Care

Design thinking is a user-centered approach to innovation that considers and integrates the needs of people within the possibilities and reach of technology [31,32]. Design thinking is not just for designers—it is a mindset and process of problem solving that aims to identify the core tenets that drive a specific behavior. This knowledge is then used to solve complex problems and find desirable solutions. The emerging trend of applying user-centered design to health care problems has generated promising results [33]. Skinner et al [34] employed a user-centric approach in developing a youth smoking prevention and cessation website and demonstrated in a large-scale RCT that the intervention yielded positive effects. The Center for Innovation at the Mayo Clinic uses design thinking as a core process in creative problem solving that goes beyond process analysis and quality improvement [35]. The Innovation Consultancy at Kaiser Permanente used design thinking to improve the quality of patient care during nursing shift changes [36]. The Venice Family Clinic, a community health care center in California, used the design thinking process to redesign their clinic and patient experience for low-income families [37].

#### Design Thinking Processes

There are many variations of user-centered design processes, but they all uphold the same core tenets of being human-centered, prototype-centric, and iterative. The design thinking model presented by Kembel [38], notably different for its explicit treatment of empathy, is most relevant for the goals of this study. In this model, empathy arises from a deep understanding of the stakeholders and their needs and requires an anthropological approach to understanding users and their environments. In this study, we will leverage the design thinking process presented by Kembel to create and distribute a digital intervention for English- and Spanish-speaking low-income smokers. The model consists of a 5-step cyclic process.

Empathize: fully understand the experience of the intended user via observation, interaction, and immersion in their experiences. This entails understanding their lifestyle, physical and emotional needs, how and why they do things, and what is meaningful to them as it relates to their smoking behavior. The goal is to uncover insights that will guide design and distribution of our digital intervention.Define: process and synthesize data collected from the Empathize step to outline connections and patterns of our target users. The goal is to develop a defined, meaningful, actionable problem statement that will provide focus when developing and evaluating proposed solutions.Ideate: generate a variety of possible solutions to provide source material for building prototypes. It is critical during this step to defer judgment and push for a wide range of ideas, allowing us to think beyond obvious existing solutions. The best solution is eventually determined during the prototyping and testing steps. We propose to systematically involve smokers and their health care providers in this step.Prototype: transform ideas into physical forms so users can interact with them. Initial low-fidelity prototypes (eg, sketch drawings, storyboards) are quick and inexpensive ways for the team to learn how well a solution aligns with the user needs. Each iteration moves the team closer to a final, user-defined solution.Test: observe and elicit feedback to learn more about the user, refine prototypes, and gain clarity on how well the solution addresses the problem statement.

### Research Design and Methods

#### Framework

##### Human-Centered Development

We will develop iterative versions of digital interventions for smoking cessation in Spanish and English that are highly responsive to the needs and preferences of low-income and Latino smokers. Development will take place with user input from patients who are part of the SFHN. We will use the 5-step cyclic design thinking process described above to understand low-income smokers and iteratively develop and refine an effective digital smoking cessation Web app that they will use.

##### Dissemination Strategies

We will include in the ethnographic semistructured interviews questions regarding how the users found out about Web apps installed on their phones, how they use text messaging, and which digital smoking cessation tools they have used the most (if any). This information will guide the development of our recruitment and dissemination strategies both at the SFHN and at the state level.

##### Evaluation of the San Francisco Stop Smoking Web App

We will develop a baseline Web app and 3 successive versions of the user-centered Web app, the last of which will be evaluated in an RCT.

#### Initial Ethnography (Empathy Step)

##### Recruitment

We will recruit 60 low-income participants aged 18 years or older who are members of the SFHN, use smartphones, and have been advised by their care providers to quit smoking or have tried to quit smoking at least once. They will be divided into four target groups (15 English-speaking men, 15 English-speaking women, 15 Spanish-speaking men, 15 Spanish-speaking women). These 60 participants will be asked to sign consent to participate in the shadowing process and short or in-depth interviews conducted by research assistants. We will also recruit 10 health care providers from the SFHN (eg, smoking cessation counselors, nurses, physicians) to contribute to the Ideate step by taking part in a prototyping exercise (see Figure 1, Field Study 3).

**Figure 1 figure1:**
[figure not shown]
Flow of research study.

##### Methods

To ensure that our solution is based on a solid foundation, we will invest significant efforts during the initial Empathy step to understand our users. We will employ ethnographic methods to build a deep understanding of low-income English- and Spanish-speaking smokers. Research assistants will receive ethnography training (manuals and mock interviews) prior to going out into the field. We will conduct semistructured interviews pertaining to our themes of interest. Short interviews are hour-long semistructured interviews where research assistants will recruit patients from SFHN clinic waiting rooms to ask a set of questions related to their lifestyle and smoking habits. In-depth interviews will include a short interview plus a follow-up interview after a quit attempt and shadowing period of 3 hours in a natural location for the participant. Relevant themes include behaviors related to smoking, technology usage, personal lifestyle and social circles, how they get information (informing dissemination strategies), and personal values and motivations. All interviews will be audiorecorded and sent to third-party services for transcription.

##### Outputs and Qualitative Analysis

Our ethnographic methods will yield a large amount of transcribed material, screenshots, and other photographs showing the use of apps. Our qualitative analysis will involve developing and refining our themes, identifying quotes from participants that support each theme, and developing a coding system that will help us identify behavior patterns and draw conclusions that will inform the next step in the design process.

#### Implementing the User-Centered Design

##### Recruitment

SFHN patients will be recruited by research assistants at outpatient clinics. We will seek patients who own smartphones and intend to quit smoking in the next 3 months who either have been advised to quit smoking by their care provider or have tried to quit smoking at least once. Patients will be paid $25 per hour for their time for interviews as described in face-to-face studies below.

##### Procedures

User-centered design, development, and testing will be carried out as shown on Figure 1, with two interconnected processes running in parallel: face-to-face user input from SFHN smokers via ethnographic and field test methods and online studies that will include samples recruited from the SFHN and open online recruitment. In all studies, half of the participants will be English-speaking and half Spanish-speaking.

